## Abstract

**Background:**

Postpartum hemorrhage (PPH) is the leading cause of maternal mortality worldwide and accounts for one third of maternal deaths in low-income and middle-income countries. PPH can be prevented by active management of the third stage of labor (AMTSL), a series of steps recommended by the World Health Organization to be performed by skilled birth attendants (SBAs). Task shifting in the AMTSL step of uterotonic drugs administration to community health workers, traditional birth attendants and self-administration has been investigated as a strategy to increase access to quality obstetric care considering persistent SBA and facility-based delivery shortages. The aim of this study is to assess task shifting in the final step of AMTSL and compare uterine tonus assessment by a SBA to self-assessment.

**Methods and Design:**

The study is an individual-level two-arm non-inferiority randomized controlled trial (RCT). A total of 800 women will be recruited in Korle Bu Teaching Hospital in Accra, Ghana. Adult women in labor at term with an expected vaginal delivery who received antenatal instructions for self-assessment of uterine tonus will be eligible for inclusion. Women with an increased risk for PPH will be excluded. Women will be randomized to uterine tone assessment by a skilled birth attendant (midwife) or uterine tone self-assessment (with the safety back-up of a midwife present in case of PPH or uterine atony). Postpartum blood loss will be measured through weighing of disposable mats. The main study endpoints are PPH (≥500 ml blood loss), severe PPH (≥1000 ml blood loss), mean blood loss, and routine maternal and neonatal outcomes. Participants and caregivers will not be blinded given the nature of the intervention.

**Discussion:**

A reduction of PPH-related maternal mortality requires full implementation of AMTSL. Task shifting of uterine tone assessment may contribute to increased AMTSL implementation in (clinical) settings where SBAs capacity is constrained.

**Trial registration:**

Clinicaltrials.gov: NCT02223806, registration August 2014. PACTR: PACTR201402000736158, registration July 2014. University of Ghana, Medical School Ethical and Protocol Review Committee: MS-Et/M.8–P4.1/2014-2015

**Electronic supplementary material:**

The online version of this article (doi:10.1186/s13063-015-1111-5) contains supplementary material, which is available to authorized users.

## Background

### Postpartum hemorrhage is the leading cause of maternal death

Each year, approximately 287,000 women die because of preventable causes related to pregnancy and childbirth [1]. Almost all (99 %) of these deaths occur in low-income and middle-income countries (LMIC), with the largest burden in sub-Saharan Africa and South Asia [1].

The most common cause of maternal death is postpartum hemorrhage (PPH), defined as blood loss equal to or greater than 500 ml within 24 h after birth of the infant. PPH occurs in around 10.5 % of all deliveries and is responsible for more than 130,000 deaths annually [2, 3]. In sub-Saharan Africa, 33.9 % of maternal deaths are due to PPH [4].

The maternal mortality ratio of Ghana in 2013 was 380 maternal deaths per 100,000 live births [5]. The leading cause of maternal deaths was obstetric hemorrhage, with estimates ranging between 27 and 32 % [6–10].

Causes of PPH include uterine atony, uterine rupture, incisions, lacerations and coagulopathy, with uterine atony being the most common cause of PPH. Risk factors for atony include multiparity (five or more deliveries), polyhydramnios, fetal macrosomia, abnormal placentation, placental abruption, induced or prolonged labor and retained placental tissue [2, 11].

### AMTSL can prevent PPH

Whether a woman dies from PPH depends largely on access to timely and competent obstetric care [12]. PPH mostly occurs during the third and fourth stages of labor [2, 13], and active management of the third stage of labor (AMTSL) can prevent its occurrence. AMTSL is recommended as a series of steps performed by skilled birth attendants (SBAs) by the World Health Organization (WHO) and the international professional organizations of gynecologists and midwives [2, 13, 14]. The steps include the provision of uterotonic drugs (oxytocin or misoprostol) immediately upon fetal delivery, controlled cord traction, massage of the fundus of the uterus immediately after placental delivery in the absence of uterotonics, and routine assessment of the uterine tonus every 15 min for the first 2 h postpartum.

### Task shifting in AMTSL

AMTSL when performed by SBAs is the “gold standard” for prevention of PPH [2, 15] and can reduce excessive blood loss by 50–70 % [16]. This provides a challenge in many LMIC where the majority of women live in rural areas and deliver at home without SBAs available, often assisted by traditional birth attendants or family members who are not educated in obstetric care [17]. Task shifting of AMTSL to community health workers, traditional birth attendants, or self-administration has been explored as a strategy to increase access to quality obstetric care in response to the obstacles [18].

Of all AMTSL interventions, uterotonic drugs are the most effective in preventing PPH, although the relative contribution of each of the AMTSL components has not been well-studied [2, 19]. Oxytocin is the preferred uterotonic drug. However, as oxytocin is thermo-unstable, requires refrigeration and should be injected by SBAs, misoprostol is considered a safe, cheap and only slightly less effective alternative [20–23]. The WHO recommends the provision of misoprostol by community health workers for PPH prevention in rural areas and homebirths in absence of SBAs [2, 13]. The community distribution of misoprostol for self-administration by women is also widely explored as an option, but currently not recommended [24–26]. Controlled cord traction is contraindicated without assistance of a SBA [2]. To the best of our knowledge, there is currently no research or recommendation about the relative contribution of uterine tonus assessment for the prevention of PPH available, or the effect of task shifting of uterine tonus assessment [2, 13, 27]. Therefore, the aim of this non-inferiority randomized controlled trial (RCT) is to determine whether there is a difference in outcomes following routine uterine tone assessment every 15 min in the first 2 h postpartum performed by a SBA (midwife) compared to self-assessment by a patient.

## Methods/Design

### Study design

This study will be a pragmatic non-inferiority individual-level two-arm RCT comparing two strategies of AMTSL.

### Participants

The population base for the current study is pregnant women admitted in labor at Korle Bu Teaching Hospital (KBTH). KBTH has approximately 10,600 deliveries every year, approximately 200 per week. AMTSL has been implemented at KBTH. As a result of midwife understaffing, the routine assessment of the uterine tone for the first 2 h postpartum has been delegated to patients who received adequate training during the antenatal care (ANC) visits and who receive a repeated instruction after delivery. These women are regularly monitored by midwives. Yet, whether this task shifting is indeed equally effective has not been formally evaluated.

#### Inclusion criteria

In order to be eligible to participate in this study, the following criteria must be met: be at least 18 years of age, in labor with an expected vaginal delivery of a term singleton gestation, and recipient antenatal instructions on postnatal uterine tonus self-assessment.

#### Exclusion criteria

The following criteria will result in exclusion from study participation: operative delivery, severe anemia (<8 g/dL) within 2 weeks of delivery, risk factors for PPH (history of previous PPH, palpable uterine myoma, antepartum hemorrhage, anticipated breech delivery), intra uterine fetal death.

### Intervention

Participants will be randomly assigned to one of the two arms:uterine tonus assessment by patient, every 15 min for the first 2 h (current standard practice).uterine tonus assessment by a SBA (midwife), every 15 min for the first 2 h (guideline recommended practice).

### Study objectives and hypothesis

#### Primary objective

To determine whether there is a difference in incidence of PPH (≥500 ml blood loss) following routine uterine tone assessment every 15 min in the first 2 h postpartum performed by a SBA (midwife) compared to self-assessment by a patient.

#### Secondary objective

To determine whether routine uterine tonus assessment every 15 min in the first 2 h postpartum when performed by a SBA (midwife) compared to self-assessed by a patient, results in differences in incidence of severe PPH (≥1000 ml blood loss), differences in mean blood loss, use of additional uterotonics, use of other procedures for management of PPH (surgery, manual placenta tissue removal), blood transfusion, maternal resuscitation and maternal death.

#### Other study endpoints and parameters

Neonatal outcomes will be assessed by: Apgar scores at 1 and 5 mins, neonatal resuscitation or perinatal death.

The following socio-demographic and obstetric characteristics will be collected: age, marital status, employment, education, number of previous pregnancies, number of previous deliveries (live births and still births), number of children, present pregnancy history, medical and surgical history.

#### Hypothesis

It is hypothesized that there will be no difference in outcomes for the SBA-assessed group compared to the self-assessment arm.

### Sample size calculation and justification

PPH has an incidence of approximately 11.1 % in the Ghanaian population [28]. The hypothesis of this non-inferiority RCT is that there is no difference between the two treatments. To exclude a difference of between 5 to 7.5 % with a 1-sided alpha co-efficient of 5 % at a power of 80 %, between 978 and 436 participants would have to be randomized [29]. Given resource restrictions, our sample size will be 800 women, and powered to exclude a difference of 5.53 %.

As the intervention and outcome assessment take place on the same day, we expect no loss to follow-up.

### Study procedures

#### Recruitment and enrollment

Enrollment will take place at the ANC clinic and on the antenatal wards of KBTH after informed consent has been provided. Information about the study will be available at the ANC clinic and provided during the ANC education/training for uterine tonus assessment to familiarize women with the study (see Additional file 1 for the Standardized Operating Procedure for the training). Patients will be screened for eligibility based on the previously stated inclusion and exclusion criteria by trained research assistants. All patients will receive antenatal education on uterine tonus self-assessment.

#### Randomization, treatment allocation, and treatment concealment

Randomization occurs at presentation at the labor ward in established labor. If at this stage enrolled patients present with one of the exclusion criteria, they will be excluded from the study.

Participants will be assigned a study identification code based on consecutive enrollment. After the identification number has been assigned to a participant, a matching sealed opaque envelope in which the arm allocation is concealed can be opened by the research assistant. Women will be assigned an allocation arm while in labor, but before the onset of birth to facilitate the understanding of the arm they were allocated – as at time of full dilation or start of pushing, the ability to absorb the new information may have been reduced compared to an earlier stage of labor. The randomization list with blocks ranging between 2–6 identifiers will begenerated by the Data Management Department of the University Medical Center Utrecht using SAS software (SAS Inc., Cary, NC, USA). Additional randomization codes can be created to replace women who were excluded from the study because of complications, including caesarian sections.

Because of the nature of the intervention patients, care providers and research assistants will not be blinded.

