### Statistical analysis

Descriptive statistics for participant characteristics (age, marital status, employment, education, number of previous pregnancies, number of previous deliveries (live births and still births), number of children, present pregnancy history, medical and surgical history) will be presented as frequencies and percentages for dichotomous and categorical variables, and means and standard deviations for continuous variables will be presented. Differences between treatment groups will be assessed using Student’s *t* test for continuous outcome data and the chi square test for discrete outcome data, and reported significant with a *p* value of < 0.05.

Analyses for the first and second research objectives between intervention group and outcomes will be according to intention-to-treat. Primary and secondary dichotomous, categorical and continuous outcome variables will be descriptively analyzed in an approach similar to the participant characteristics analysis.

For the blood loss-related outcomes of interest (PPH, severe PPH and mean blood loss), linear and logistic regression analysis will be used to analyze the difference between the two arms. Participant characteristics with significant differences between the two groups despite randomization will be considered confounders in a multivariate logistic or linear regression analysis. The lower limit of the 90 % confidence interval on the difference between the groups in frequency of the primary outcome will be used to assess non-inferiority for these three variables. Observations with missing outcome data will not be considered in these analyses.

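### Women already allocated can be excluded for undefined complications and replaced, with no time cut-off, so the analysis set is not the intention-to-treat set that the plan names

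*Protocol article*

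**What the plan says.** Four statements in the protocol article bear on this.

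- **Exclusion criteria:** "The following criteria will result in exclusion from study participation: operative delivery", followed by severe anaemia, risk factors for PPH (antepartum haemorrhage among them) and fetal death in utero.
- **Randomization, treatment allocation, and treatment concealment:** the envelope is opened during labour and before birth. Women who meet an exclusion criterion on presentation at the labour ward are removed. The section then adds: "Additional randomization codes can be created to replace women who were excluded from the study because of complications, including caesarian sections". It also says that patients, care providers and research assistants are not blinded.
- **Statistical analysis, population:** "Analyses for the first and second research objectives between intervention group and outcomes will be according to intention-to-treat".
- **Statistical analysis, missing data:** "Observations with missing outcome data will not be considered in these analyses".

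No modified intention-to-treat set is named.

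**The concern.** The replacement sentence and the intention-to-treat sentence cannot both hold. Replacement codes are needed only where a code has been used, so the sentence concerns randomised women who are taken out and not analysed.

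Three features make this more than a matter of labelling:

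1. Caesarean section is given as one example of a complication, and no other is defined.
2. No point in time is set after which exclusion stops.
3. The people who would decide know the allocated arm.

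As written, the rule does not exclude a decision taken after birth for a reason connected with bleeding. In a non-inferiority trial, the loss of events from the self-assessment arm moves the result towards the conclusion sought. New women recruited in place of those removed restore the number but not the lost events.

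**Working it through.** **1. The plan's own figures.** Inputs, all from Sample size calculation and justification: "PPH has an incidence of approximately 11.1 % in the Ghanaian population"; the test is "with a 1-sided alpha co-efficient of 5 % at a power of 80" per cent; "between 978 and 436 participants would have to be randomized" for differences of 5 % and 7.5 %; and "our sample size will be 800 women, and powered to exclude a difference of 5.53" per cent. Equal allocation, 400 per arm, is assumed.

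Formula: n per arm = 2 × p(1 − p) × (1.645 + 0.842)² / margin², with p = 0.111.

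| Margin | n per arm | Total | Stated |
|---|---|---|---|
| 5 % | 488.1, rounded up to 489 | 978 | 978 |
| 7.5 % | 216.9, rounded up to 217 | 434 | 436 |
| 5.53 % | 399.0, rounded to 399 | 798 | 800 |

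The sample size arithmetic reproduces. The problem is the analysis population, not the number of women.

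**2. Which women the replacement sentence concerns.**

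- Allocation comes before birth, and the postpartum assessment comes after it.
- Operative delivery that is already planned is screened out, because entry requires an expected vaginal delivery and there is a further check on the labour ward. Unplanned operative delivery can arise only after that check, so some post-randomisation exclusion is built in.
- The sentence does not stop there. It covers complications in general, at any time.

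**3. What selective loss would do.** The document gives no number of exclusions, so the losses below are assumptions. Take the true rates at the margin: midwife arm 11.1 %, self-assessment arm 11.1 % + 5.53 % = 16.63 %. Expected PPH cases are 400 × 0.111 = 44.4 and 400 × 0.1663 = 66.5.

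For k cases removed from the self-assessment arm, its observed rate is r = (66.52 − k)/(400 − k). With d = r − 0.111 and SE the unpooled standard error of the difference,

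P(false non-inferiority) = Φ((0.0553 − d)/SE − 1.645).

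*Loss from the self-assessment arm only:*

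| k | Share of that arm's cases | r | d | SE | False non-inferiority |
|---|---|---|---|---|---|
| 0 | 0 % | 16.63 % | 5.53 % | 2.436 % | 5.0 % |
| 4 | 6 % (4/66.5) | 15.79 % | 4.69 % | 2.413 % | 9.7 % |
| 8 | 12 % (8/66.5) | 14.93 % | 3.83 % | 2.389 % | 17.5 % |

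For k = 4: (0.0553 − 0.0469)/0.02413 − 1.645 = −1.296, and Φ(−1.296) = 0.097. Refilling the arm to 400 with women at the observed rate r changes SE only slightly and gives nearly the same results (9.8 % and 17.7 %).

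*The same fraction lost from both arms:*

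| Fraction lost | Midwife cases lost | d | SE | False non-inferiority |
|---|---|---|---|---|
| 6 % | 2.7 | 5.29 % | 2.392 % | 6.1 % |
| 12 % | 5.3 | 5.03 % | 2.345 % | 7.6 % |

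Most of the inflation therefore comes from assuming that the loss is confined to one arm.

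**The case against.** The strongest reply is that the harmful reading sits badly with the protocol's own objectives. The secondary objective counts severe PPH, additional uterotonics, surgery, manual removal of placental tissue, transfusion, resuscitation and maternal death as outcomes. Excluding women for such events would empty that objective. The more natural reading is of events in labour that end eligibility, such as an unplanned caesarean section, and those precede the assessment being compared. This stands. A reader might infer that the plan intends to drop women who bleed, or that events will leave the self-assessment arm. The document states neither; its wording only fails to prevent it.

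The reply has a second part: the complete-case rule is a common one, and few outcomes should be missing. Blood is weighed over the first two hours after birth and the protocol expects no loss to follow-up. This also stands. A reader might picture a woman taken to theatre before her mats are weighed, but nothing in the document describes such a case. The missing-data sentence is a minor matter beside the exclusion rule.

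What the reply does not remove is the conflict between two stated rules. Even on the benign reading, randomised women are excluded and replaced, which is not intention-to-treat. Nor is this detail left to a fuller document, since the article itself states both rules.

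**Conclusion.** The point holds in a limited form and should be fixed. The stated analysis population is wrong as labelled, and the exclusion rule is open-ended, has no time limit and is applied by people who know the arm.

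The effect on error is a conditional worst case. It rests on a true difference at the 5.53 % margin, 400 women per arm, the normal approximation, and losses that are assumed rather than documented. Under those assumptions the one-sided 5 % error becomes about 10 % or 18 % if 4 or 8 cases vanish from the self-assessment arm alone, and about 6 % or 8 % if the same fractions vanish from both. The larger figures should not be read as the expected error of this trial, because nothing in the document supports loss from one arm only. If exclusions were confined to events before birth and did not depend on arm, little bias would be expected and the remaining fault would be the label.

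**What to change.** 1. **Randomization, treatment allocation, and treatment concealment:** replace the sentence on additional codes with wording to this effect:

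> After allocation, a woman is excluded only for operative delivery or another listed exclusion criterion that arises before birth of the infant. She may be replaced. No woman is excluded or replaced for any event after birth.

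   Reconcile this with Exclusion criteria, which names operative delivery without limiting it to caesarean section, so that both sections use the same term with the same meaning.

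2. **Statistical analysis, population:** name the set modified intention-to-treat, defined as all randomised women still eligible at birth, analysed in the arm allocated. State that exclusions will be accounted for by arm and reason.

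3. **Statistical analysis, missing data:** add one sensitivity analysis that counts any missing blood loss in the self-assessment arm as PPH. Do not infer PPH from the use of additional uterotonics. That departs from the 500 ml endpoint, and in an open-label trial such use could itself differ by arm.

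The cost is a few sentences, a count of exclusions by arm and one small extra analysis. A few complicated cases will stay in the analysis. Neither the treatment nor the target of 800 women changes.

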#### Blood loss estimation

Assessment of blood loss will be performed by trained midwives by weighing blood collected after delivery of the placenta using disposable mats (“INCO pads”) of 90 x 60 cm. Scales will be standardized and calibrated. Blood loss will be measured up to 2 h postpartum.

#### Other outcomes

All other maternal endpoints will be obtained from maternal record books, surgery record books, antenatal booklet and interviews.

#### Disposal of medical waste

Mats used in the study will be disposed according to the standard procedures of disposal of medical waste at KBTH.

#### Standard of care during study participation

Participants will receive the standard of care during their participation in the study, including all standard care at KBTH associated with the development, prevention or treatment of PPH. Women who report inadequate uterine contraction to their midwife, will receive the standard of care according to PPH protocols of KBTH.

#### Handling and storage of data and documents

Data will be handled confidentially and anonymously through assigning a consecutive numeric identification (ID) code to participants. A separate subject identification list will be used to link the participant ID code to the participant names.

The local investigator(s) have access to the source data. The key to the code will remain with the coordinating investigator. In accordance to Good Clinical Practice rules, the dataset will be stored for 15 years.

### Statistical analysis

Descriptive statistics for participant characteristics (age, marital status, employment, education, number of previous pregnancies, number of previous deliveries (live births and still births), number of children, present pregnancy history, medical and surgical history) will be presented as frequencies and percentages for dichotomous and categorical variables, and means and standard deviations for continuous variables will be presented. Differences between treatment groups will be assessed using Student’s *t* test for continuous outcome data and the chi square test for discrete outcome data, and reported significant with a *p* value of < 0.05.

Analyses for the first and second research objectives between intervention group and outcomes will be according to intention-to-treat. Primary and secondary dichotomous, categorical and continuous outcome variables will be descriptively analyzed in an approach similar to the participant characteristics analysis.

For the blood loss-related outcomes of interest (PPH, severe PPH and mean blood loss), linear and logistic regression analysis will be used to analyze the difference between the two arms. Participant characteristics with significant differences between the two groups despite randomization will be considered confounders in a multivariate logistic or linear regression analysis. The lower limit of the 90 % confidence interval on the difference between the groups in frequency of the primary outcome will be used to assess non-inferiority for these three variables. Observations with missing outcome data will not be considered in these analyses.

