#### Benefits and risks assessment

There are no direct benefits or incentives for participants who participate in this study. As the intervention group receives a midwife assessment of uterine tonus, the benefit of participating in this study is that PPH may be detected slightly earlier than may otherwise be the case. As the study takes places at the labor ward, the control arm will receive the same quality of care and will be monitored by the midwives as part of routine care. Because most of the data will be collected from collection books, the time investment is minimized as much as possible.

All participating women are enrolled in the national health insurance scheme. No data safety monitoring board was installed for this study. Details about safety reporting are available upon request.

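### The article rests the non-inferiority conclusion on intention-to-treat alone, so midwife checks missed in the SBA arm would favour the claim without being visible

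*Protocol article*

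**What the plan says.** The Study design section sets the frame: "This study will be a pragmatic non-inferiority individual-level two-arm RCT comparing two strategies of AMTSL". The Statistical analysis section fixes the analysis set: "Analyses for the first and second research objectives between intervention group and outcomes will be according to intention-to-treat". For the non-inferiority decision, the same section gives this rule: "The lower limit of the 90 % confidence interval on the difference between the groups in frequency of the primary outcome will be used to assess". The article mentions no per-protocol, as-treated or other adherence-based analysis.

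Four other places bear on how far the two arms will differ in practice:

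- Participants: "As a result of midwife understaffing, the routine assessment of the uterine tone for the first 2 h postpartum has been delegated to patients".
- Intervention: checks every 15 minutes for two hours in both arms. Self-assessment is labelled as what the hospital does now, and midwife assessment as what the guideline recommends.
- Recruitment and enrollment: "All patients will receive antenatal education on uterine tonus self-assessment".
- Benefits and risks assessment, on the self-assessment arm: "the control arm will receive the same quality of care and will be monitored by the midwives as part of routine care". The Abstract also describes self-assessment as having a midwife available as back-up.

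The sample size section attributes the choice of 800 women to limited resources. The article does not say how the SBA arm will be staffed and gives no expected adherence.

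**The concern.** In a superiority trial, non-adherence that makes the arms alike works against the claim, so intention-to-treat is the cautious choice. In a non-inferiority trial the same dilution works for the claim.

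The SBA arm asks midwives for 120/15 = 8 checks per woman, or 8 × 400 = 3,200 checks if allocation is 1:1. This is the task that the ward had passed to patients because it lacked midwives. Some missed checks in that arm are therefore plausible. Every woman has been trained to self-assess, so one whose midwife check is missed may simply do it herself.

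The trial could then find the arms similar because guideline practice was not delivered, rather than because self-assessment is as good. With intention-to-treat as the only set and no adherence measure described, a reader could not tell these two explanations apart.

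**Working it through.** **Inputs.** From the sample size section: PPH incidence 11.1 %, one-sided alpha 5 % (z = 1.645), power 80 % (z = 0.842), 800 women, excludable difference 5.53 points. Assumptions: 1:1 allocation (400 per arm); 5.53 points treated as the margin M; f, the share of the SBA arm that in effect only self-assesses, for which the article gives no value.

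**Step 1: the plan's own figures.** With equal rates p = 0.111 in both arms, n per arm = (1.645 + 0.842)² × 2p(1 − p) / margin², where 2 × 0.111 × 0.889 = 0.19736.

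- Margin 0.05: 489 per arm, 978 in total (stated 978).
- Margin 0.075: 217 per arm, 434 in total (stated 436).
- With 400 per arm: margin = √(0.19736 × 2.487² / 400) = 5.52 points (stated 5.53). Power at 5.53 points is 80.1 %.

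The figures reproduce. The calculation contains no allowance for lost contrast.

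**Step 2: effect of missed midwife checks on intention-to-treat.** Let self-assessment be truly worse by exactly M = 0.0553, so that a correct test claims non-inferiority 5 % of the time. A share f of the SBA arm takes the self-assessment risk. Then:

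- SBA-arm risk: p_S = p_SBA + f × M
- observed difference (self minus SBA): d = M(1 − f)
- SE = √[p_S(1 − p_S)/400 + p_self(1 − p_self)/400]
- chance of claiming non-inferiority = Φ[(M − d)/SE − 1.645]

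Worked case, f = 0.2 with p_SBA = 0.111 and p_self = 0.1663: p_S = 0.1221, d = 0.0442, SE = 0.0248, so Φ(0.0111/0.0248 − 1.645) = 0.115.

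The 11.1 % could belong to either arm, so both cases are shown.

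| f (assumed) | ITT difference (points) | False claim, SBA risk 11.1 % | False claim, self-assessment risk 11.1 % |
|---|---|---|---|
| 0 | 5.5 | 5.0 % | 5.0 % |
| 10 % | 5.0 | 7.8 % | 8.6 % |
| 20 % | 4.4 | 11.5 % | 13.7 % |
| 30 % | 3.9 | 16.3 % | 20.3 % |
| 50 % | 2.8 | 28.9 % | 37.3 % |

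**Step 3: power of a supporting per-protocol analysis.** Drop the non-adherent SBA-arm women and keep 400 in the other arm, with a true risk of 11.1 % in both. Power = Φ[0.0553/√(0.111 × 0.889 × (1/(400(1 − f)) + 1/400)) − 1.645]. This gives 78.2 % at f = 10 %, 75.9 % at 20 % and 73.1 % at 30 %.

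**Step 4: why the per-protocol definition matters.** A simple rule would require most of the 8 checks to be done by the allocated assessor. When a self-assessing woman bleeds or reports poor contraction, a midwife steps in, so she could fail the rule because of the outcome. An SBA-arm woman who bleeds still has her allocated assessor. Suppose 20 % of the self-assessment arm's PPH cases were dropped in this way. Its risk would become 0.1663 × 0.8 / (1 − 0.1663 × 0.2) = 0.1376, and the difference from 0.111 would fall from 5.5 to 2.7 points. Such a set would be more biased towards non-inferiority than intention-to-treat at f = 30 %, where the difference is still 3.9 points.

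**The case against.** The strongest reply is that the article nowhere predicts dilution. The staffing remark describes routine care before the trial, and the SBA arm is defined as midwife assessment at every scheduled time. This stands: missed checks are an inference from the staffing history and current practice, not the document's own view.

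Several stronger readings are tempting but not supported:

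- *Midwife monitoring of the self-assessment arm is contamination.* It is not. Monitoring and back-up belong to the strategy under test, in a trial that calls itself pragmatic. They limit how far the result carries to settings without midwives, but they are not non-adherence, and a per-protocol set would not remove them.
- *Training every woman is crossover.* Training comes before randomization and is an inclusion criterion. It matters only where a midwife check is missed.
- *The bias can run only one way.* Self-checks that women miss would, if checks matter, worsen the self-assessment arm and work against the claim.
- *No per-protocol analysis exists.* Only the condensed article is at hand, and it says that a full protocol is available on request. All that can be said is that the article names none.

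It is also fair to object that the error rates rest on assumed shares, on a true effect exactly at 5.53 points, and on affected women losing all the benefit of midwife checks. What remains is that the published rule lets intention-to-treat alone carry the claim, with a documented reason to doubt full delivery of the SBA arm. The pragmatic label does not settle this, because a claim of non-inferiority to guideline practice needs evidence that guideline practice was delivered.

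**Conclusion.** The point holds in a limited form. Intention-to-treat is a proper primary analysis here; the weakness is that it is the only set named for a non-inferiority decision. Missed midwife checks are plausible from the article's account of staffing and current practice, and they would favour the claim. At a true excess of 5.53 points, a loss of 10 to 30 % of the SBA-arm contrast takes the one-sided error from 5 % to roughly 8 to 20 %. With full adherence there is no inflation from this source. The direction follows from the design; the size depends on an adherence rate that the article does not give. A reader might infer that the trial is bound to be biased towards non-inferiority, but the document does not support that. This should be corrected, but it does not invalidate the design.

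**What to change.** Keep intention-to-treat as the primary analysis and add the following:

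1. On the case form, record for each scheduled check whether it was done and by whom. The Trial status section says that enrollment has begun, so this can apply only to women still to be enrolled.
2. Report adherence by arm.
3. Before analysis, define a per-protocol set for the primary endpoint. Judge adherence only on checks due before any PPH, report of atony or midwife take-over, so that the outcome does not decide who is in the set. A woman with no check due before such an event stays in.
4. Describe non-inferiority as robust only if the per-protocol analysis agrees with intention-to-treat.

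If the full protocol already contains such a set, cite it in the article and check that its definition meets item 3.

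The cost is one entry per check and one further analysis. The supporting set is smaller, with power of about 78 % at 10 % and 76 % at 20 % non-adherence. Per-protocol sets can be selected, so this analysis supports intention-to-treat and does not replace it. Adherence data will be incomplete for women already enrolled, and the report should say so.
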